## Abstract

**Background:**

Mental illness is one of the top causes of preventable pregnancy-related deaths in the United States. There are many barriers that interfere with the ability of perinatal individuals to access traditional mental health care. Digital health interventions, including app-based programs, have the potential to increase access to useful tools for these individuals. Although numerous mental health apps exist, there is little research on developing programs to address the unique needs of perinatal individuals. In an effort to fill this gap, a multidisciplinary team of experts in psychology, psychiatry, obstetrics, and pediatric primary care collaborated to develop the novel Perinatal Skills Program within Maya, a flexible and customizable cognitive-behavioral skills app. Maya-Perinatal Skills Program (M-PSP) uses evidence-based strategies to help individuals manage their mood and anxiety symptoms during pregnancy and post partum.

**Objective:**

This pilot study aims to assess the feasibility, acceptability, and usability of M-PSP and explore links between program use and symptoms of anxiety and low mood.

**Methods:**

This single-arm trial will recruit 50 pregnant or postpartum individuals with mild-to-moderate anxiety or mood symptoms. Participants will be recruited from a variety of public and private insurance-based psychiatry, obstetrics, and primary care clinics at a large academic medical center located in New York City. Participants will complete all sessions of M-PSP and provide feedback. Outcome measures will include qualitative and quantitative assessments of feasibility, acceptability, and usability, passively collected program usage data, and symptom measures assessing mood, anxiety, and trauma. Planned data analysis includes the use of the grounded theory approach to identify common themes in qualitative feedback, as well as an exploration of possible associations between quantitative data regarding program use and symptoms.

**Results:**

The recruitment began on August 2023. As of October 2024, a total of 32 participants have been enrolled. The recruitment will continue until 50 participants have been enrolled.

**Conclusions:**

Digital health interventions, like M-PSP, have the potential to create new pathways to reach individuals struggling with their mental health. The results of this study will be the groundwork for future iterations of M-PSP in the hopes of providing an accessible and helpful tool for pregnant and postpartum individuals.

**Trial Registration:**

ClinicalTrials.gov NCT05897619; https://classic.clinicaltrials.gov/ct2/show/NCT05897619

**International Registered Report Identifier (IRRID):**

PRR1-10.2196/59461

## Introduction

Maternal mental health plays a pivotal role in influencing the health and well-being of both mothers and their children. In the United States, there is a growing maternal health crisis, in which mental health conditions rank among the top causes of preventable pregnancy-related deaths for mothers [1,2]. During pregnancy and the postpartum period, perinatal mood and anxiety disorders (PMADs) significantly influence a mother’s ability to function, care for, and bond with their newborn, which can have an impact on the child’s subsequent socioemotional developmental trajectory [3-5].

Though PMADs remain prevalent, with global perinatal depression rates at 26.3%, there is a serious lack of effective, accessible, and affordable mental health care for individuals in the perinatal period [6]. This is particularly true in low- and middle-income communities and countries. In these areas, a general scarcity of maternal mental health services is further exacerbated by stigma, fewer financial resources, and logistical barriers that interfere with connecting to care [7]. As such, many struggling individuals suffer in silence, without appropriate recognition or intervention for their pressing maternal mental health needs [8].

Fortunately, the digital age offers a beacon of hope in bridging the divide between growing community needs and barriers to care, and digital health interventions have the potential to improve maternal mental health outcomes [9]. Specifically, smartphone apps may be able to offer accessible and user-friendly platforms that teach useful coping strategies, which may be especially beneficial for mothers who have difficulty accessing traditional mental health services [10]. However, the landscape of mobile health apps using evidence-based information or psychological interventions is relatively sparse, and efforts to tailor these tools to meet the unique needs of the perinatal population are in the early stages of the field [11,12]. There are numerous mobile health apps targeting this population, with a range of tools for prevention, screening, and treatment, and varying content that includes psychoeducation, symptom monitoring, cognitive behavioral therapy (CBT), mindfulness, and attention bias modification training. Thus far, evidence regarding the effectiveness of existing mobile health interventions is mixed. Recent meta-analyses and systematic reviews demonstrate that app-based interventions are effective for individuals with mild-to-moderate symptoms of perinatal depression and anxiety and may be effective at preventing and treating postpartum depression compared to control groups [12,13]. Few of the existing apps use both evidence-based strategies and provide psychoeducation, as well as target both pregnant and postpartum individuals and both depression and anxiety. More research is needed to aid in the development of technology that is feasible, acceptable, and effective for pregnant and postpartum individuals who need tools to support their mental health.

To help address the critical gap in care needs, this study will present a protocol to assess the feasibility and acceptability of the novel Perinatal Skills Program within Maya, a cognitive-behavioral skills app. Maya-Perinatal Skills Program (M-PSP) is a 12-session mobile app–based program teaching evidence-based strategies to manage mood and anxiety symptoms for perinatal individuals. Following a community-based participatory research model, the study team is seeking feedback from users throughout the early stages of program development. User input will help inform future iterations of the app-based program in hopes of creating a tool that can effectively meet the needs of this population. This protocol represents the first step in the development of a tool designed to increase access to evidence-based skills for individuals with PMADs.

## Methods

### Aims

The primary aim of this study is to assess the feasibility and acceptability of M-PSP. Specifically, the team will evaluate the mobile app–based program in terms of user satisfaction, perceived use of the program, and engagement with the program. A secondary aim of the study is to look for any associations between program completion and engagement with mental health symptoms.

### Design

This study is a mixed methods open pilot trial assessing the feasibility, usability, and acceptability of M-PSP in a perinatal population. There are no comparison arms in the trial. Outcomes will include a combination of quantitative and qualitative data gathered via self-report questionnaires, interviews, and data passively collected through the app. This methodology will allow for the collection of symptom data, participant perceptions and feedback on their experience using the app, and information on app use and engagement. Results will provide information on the potential use of this program in helping pregnant and postpartum individuals manage mood and anxiety symptoms, as well as future directions for program development.

### Setting

The study is being conducted through a large academic medical center in New York City. Participants will be recruited through various departments within the medical center, including a psychiatry specialty center, primary care and pediatric settings, and obstetrics and gynecology clinics. These sites range in providing services through private pay, private insurance, or public insurance.

### Participants

The study is currently open to recruitment, with the aim to recruit 50 pregnant or postpartum individuals across all sites. In prior studies, feasibility studies often include a sample size of approximately 50 participants, which is deemed appropriate to ensure robust findings and comprehensive insights into app usability and effectiveness, balancing the need for inclusivity and accurate representation while accounting for potential participant attrition in digital mediums [14,15]. The inclusion criteria for study participation include (1) aged 18 years or older; (2) pregnant or up to 12 months post partum; (3) scoring 8-16 on the Edinburgh Postnatal Depression Scale (EPDS) [16] or 5-14 on the Generalized Anxiety Disorder-7 Scale (GAD-7) [17]; (4) able to read and speak English; (5) have access to a smartphone or mobile device capable of receiving SMS pushes and supporting Qualtrics Surveys and App (Weill Cornell Medicine); and (6) available to speak by phone or secure videoconference. The exclusion criteria include (2) safety concerns at the time of enrollment; (2) current substance use disorder; (3) current symptoms of psychosis or mania; and (4) history of bipolar or psychotic disorder.

M-PSP is designed to address mild-to-moderate anxiety and depression symptoms and may not be appropriate for more severely impaired individuals. In order to secure feedback from participants matching the app’s target population, the inclusion criteria include those scoring in the mild-to-moderate range on anxiety and depression ratings. Participants with safety concerns at the time of intake, including recent suicidal ideation or self-harm, are excluded as they are at higher risk for heightened symptoms and risk in the perinatal period. Eligibility is not impacted by receipt of clinical care outside of the study, and participants are not excluded if they are receiving concurrent treatment for depression or anxiety.

Study participants may be disenrolled from the study if they are nonresponsive to 16 outreach attempts across 4 consecutive weeks or if their pregnancy ends.

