#### Edinburgh Postnatal Depression Scale

The EPDS [16,19] is a 10-item self-report measure of mood symptoms in perinatal individuals. Responses are coded on a scale of 0=lowest severity to 3=highest severity, with 30 being the highest score possible. Cutoffs are as follows: scores 7 and below indicate depression is unlikely, scores 8-13 indicate mild depression, 14-18 indicate moderate depression, and 19 and higher indicate severe depression [20]. Cox et al [21] found that the EPDS is a valid screening scale for depression and has satisfactory sensitivity (79%) and specificity (85%).

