#### GAD-7

The GAD-7 [17] is a 7-item self-report measure assessing symptoms of anxiety. Responders indicate the frequency of symptoms on a scale of 0=not at all to 3=nearly every day, with total scores running from 0 to 21. A score of 0-4 indicates minimal anxiety, 5-9 indicates mild anxiety, 10-14 indicates moderate anxiety, and 15-21 indicates severe anxiety. Spitzer et al [17] found that the GAD-7 exhibited reliable sensitivity (89%) and specificity (82%), validating its effectiveness as a screening tool for generalized anxiety disorder.

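### The symptom inclusion criterion sets no ceiling on the second scale, so people severe on one scale qualify for a study described as mild-to-moderate

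*Protocol article*

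**What the plan says.** Inclusion criterion 3 (Protocol article, Participants) requires "scoring 8-16 on the Edinburgh Postnatal Depression Scale (EPDS) [16] or 5-14 on the Generalized Anxiety Disorder-7 Scale (GAD-7) [17"]. The four exclusion criteria are safety concerns at enrollment, current substance use disorder, current psychosis or mania symptoms, and a history of bipolar or psychotic disorder. None of them is a symptom score.

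The next paragraph of the same section gives the reason for the ranges: "M-PSP is designed to address mild-to-moderate anxiety and depression symptoms and may not be appropriate for more severely impaired individuals". It then says that, to obtain feedback from the app's target population, "the inclusion criteria include those scoring in the mild-to-moderate range on anxiety and depression ratings". The Abstract (Methods) describes the sample as "50 pregnant or postpartum individuals with mild-to-moderate anxiety or mood symptoms".

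The severity bands are in the outcome sections. For the EPDS, "scores 8-13 indicate mild depression, 14-18 indicate moderate depression, and 19 and higher indicate severe depression". For the GAD-7, 5-9 is mild, and "10-14 indicates moderate anxiety, and 15-21 indicates severe anxiety".

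**The concern.** The two ranges have upper limits, and the rationale shows that these limits are meant to keep more severely impaired people out. Because the ranges are joined by *or*, each upper limit binds only a person who is out of range on the other scale. Someone above the EPDS limit still enters through the GAD-7, and the reverse. The criterion therefore does not do what the paragraph beneath it says it does.

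What is at stake is whom the results describe. Feasibility, acceptability and usability would be reported for a mild-to-moderate perinatal population and used to revise the program before a randomized trial. If part of the sample is severe on one scale, those results mix target and non-target users. The planned correlations between symptom scores and app engagement would also include baseline scores outside the intended range.

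**Working it through.** **Inputs from the article.** EPDS runs 0-30 (31 integer scores) and GAD-7 runs 0-21 (22 scores). Entry requires EPDS 8-16 (9 scores) or GAD-7 5-14 (10 scores). Severe means EPDS 19 or more (12 scores) or GAD-7 15 or more (7 scores). The article states no figure on this point, so there is none to reproduce.

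**Step 1: what the rule permits.**
- All score pairs: 31 × 22 = 682.
- Eligible as written: 9 × 22 + 10 × 31 − 9 × 10 = 198 + 310 − 90 = 418.
- Eligible with severe depression: these must enter through the GAD-7, so 12 × 10 = 120.
- Eligible with severe anxiety: these must enter through the EPDS, so 7 × 9 = 63.
- Eligible and severe on both: 0, since neither score would be in range.
- Eligible and severe on one scale: 120 + 63 = 183 of 418.

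Examples: EPDS 25 with GAD-7 8 is eligible, and so is EPDS 10 with GAD-7 20. EPDS 22 with GAD-7 18 is not.

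**Step 2: what other wordings would permit.**
- In range on both scales (*and*): 9 × 10 = 90 pairs, 0 severe.
- In range on at least one scale, with EPDS at most 16 and GAD-7 at most 14: 17 × 15 = 255 pairs under both ceilings, less 8 × 5 = 40 pairs below both lower limits, leaves 215 pairs, 0 severe.

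So 418 − 215 = 203 eligible pairs exceed a stated ceiling. These counts show what the rule allows. They are not expected shares of participants, because score pairs are not equally likely.

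**Step 3: how many participants this could mean.** The article gives no joint distribution of scores, so this step is assumption. Bivariate normal scores were simulated, rounded and clipped to the scale limits, and the criterion was applied as written. All values within each scenario were crossed.

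| Assumed screening pool | Eligible, above a stated ceiling | Eligible, in a severe band |
|---|---|---|
| More symptomatic: EPDS mean 10-12, SD 5-6; GAD-7 mean 8-10, SD 5-5.5; correlation 0.6-0.8 | about 11-26% | about 7-19% |
| Less symptomatic: EPDS mean 6-8, GAD-7 mean 5-6, SD 4-5 for both; correlation 0.7 | about 2-8% | about 1-6% |

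Across both scenarios, 2-26% of 50 is 0.02 × 50 = 1 to 0.26 × 50 = 13 people above a ceiling. The severe share is 1-19%, or 0.01 × 50 = 0.5 to 0.19 × 50 = 9.5 people. The simulation does not apply the safety exclusion, which would remove some high scorers.

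**The case against.** **An *or* is needed.** The program addresses both anxiety and mood, and the Abstract itself says anxiety or mood symptoms. A strict *and* would shut out people with only one of the two. This stands as an argument for entry on one scale. It does not explain why the other score is unlimited, since a ceiling on each scale is compatible with *or* for entry.

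**The article condenses a fuller protocol.** A screening form may hold a ceiling that the article omits. That is possible, so only the wording is established, not that severe cases have been enrolled. But the criterion as printed still conflicts with the rationale printed below it.

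**The effect on conclusions is limited.** This is a single-arm pilot with no efficacy claim. The progression criteria in the Discussion (50% retention from screening to enrollment, 75% completing primary outcome measures) are not defined by severity. Symptom measures are taken at intake, so off-target participants can be identified later. This stands, and it keeps the point below a must-fix.

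**Two stronger readings go too far.**
- A reader might infer a safety defect from the remark that the program "may not be appropriate for more severely impaired individuals". The documents do not support that. The remark is about fit with the target users. People with safety concerns at intake, including recent suicidal ideation or self-harm, are excluded, and the Procedure section has a licensed provider contact anyone who endorses a risk item.
- A reader might also see an error in the EPDS limit of 16 falling within the moderate band of 14-18. The window 8-16 lies wholly inside the combined mild and moderate bands (8-18). A narrower window is a design choice and contradicts nothing.

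**Conclusion.** The criterion as printed admits people who are severe on one scale by the protocol's own bands, against its stated purpose. That follows from the text alone and needs no assumption.

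The number affected is uncertain: roughly 1-13 of 50 above a stated ceiling, depending almost entirely on how symptomatic the screened pool is. Recruitment spans a psychiatry specialty center as well as obstetric, primary care and pediatric settings, so neither end of the range can be ruled out. The ratio of 183 to 418 score pairs should not be read as a share of participants.

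This is a should-fix on population definition.

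**What to change.** 1. Reconcile criterion 3 with its rationale. One wording that does so keeps *or* for entry and adds that neither score may exceed its stated upper limit. The choice of wording is the sponsor's. If the full protocol or screening form already has a ceiling, stating it in the article is enough.
2. Whether or not the criterion is amended mid-recruitment, use the intake EPDS and GAD-7 scores to count enrolled participants above either ceiling. This includes the 32 enrolled by October 2024. Report how many are in a severe band.
3. Show the feasibility, acceptability and usability outcomes with and without those participants. With so few expected, this is a descriptive comparison, not a test.

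**Cost.** One amended sentence, slightly slower recruitment and one extra table. An amendment partway through would leave participants enrolled under two rules; steps 2 and 3 handle that, and they remain possible if recruitment has closed. If the 50% screening-to-enrollment criterion is counted over everyone screened, a ceiling would also lower that rate somewhat, so the denominator should be stated.

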### Outcome Measures

#### Primary Outcome Measures

##### Feedback Interviews

Feedback interviews, led by staff via phone or video calls, include open-ended questions aimed to elicit qualitative feedback on program content, structure, and functionality, as well as user engagement and satisfaction. Questions such as “What ways could the app have been better tailored to help expectant or postpartum individuals?” will be asked to have a better gauge of acceptability, while questions like “What suggestions or comments do you have about the total number of sessions?” help address the feasibility of an intervention during and after pregnancy.

##### In-App Surveys

Weekly in-app feedback surveys are self-report measures that include Likert-scale questions regarding participant experience with specific session-by-session app-based content and structure (eg, “How helpful was Cognitive Practice [TINTED or Thinking Like a Lawyer]?”; “How likely are you to review any part of Session 3 again [eg, video, exercises, or quiz]?”). In particular, questions such as “How helpful was the content for you as an individual who is pregnant or postpartum?” and “How easy was it to fit using the app into your day-to-day life?” inform us of the acceptability and feasibility of the app, respectively, throughout the study.

##### User Version of the Mobile Application Rating Scale

Whereas the in-app surveys elicit session-by-session feedback, the user version of the Mobile Application Rating Scale (uMARS) elicits more global feedback on the overall app experience. The uMARS [18] is a validated 27-item self-report questionnaire evaluating engagement, functionality, aesthetics, information, subjective quality, and perceived impact of the app-based program. In particular, engagement, aesthetics, and information subscores will be used to measure acceptability and the functionality subscale will reflect the app’s usability.

Mean scores are derived for each of these subsections, which can then be averaged to determine an overall App Quality Score. Responses are rated between 1 and 5, with 5 indicating higher levels of satisfaction. Stoyanov et al [18] found that uMARS exhibited satisfactory internal consistency (α=.90).

##### Passive Data Collection

M-PSP passively collects data, encompassing information captured without active user input, such as when sessions were completed, frequency of program usage, and program completion. These data points will serve as measures of program feasibility and user engagement.

### Secondary Outcome Measures

#### Intake Survey

Participants will complete an intake questionnaire comprising questions related to demographics, health, mental health, and pregnancy history.

#### Edinburgh Postnatal Depression Scale

The EPDS [16,19] is a 10-item self-report measure of mood symptoms in perinatal individuals. Responses are coded on a scale of 0=lowest severity to 3=highest severity, with 30 being the highest score possible. Cutoffs are as follows: scores 7 and below indicate depression is unlikely, scores 8-13 indicate mild depression, 14-18 indicate moderate depression, and 19 and higher indicate severe depression [20]. Cox et al [21] found that the EPDS is a valid screening scale for depression and has satisfactory sensitivity (79%) and specificity (85%).

#### The Edinburgh Anxiety Subscale

The Edinburgh Anxiety Subscale [22] uses items 3, 4, and 5 from the EPDS to assess levels of anxiety among perinatal individuals. A score of 5 and above indicates the presence of anxiety [23].

#### Pregnancy Symptom Tracker

The daily Pregnancy Symptom Tracker (PST) is an ecological momentary assessment tool that aims to merge and consolidate gold-standard symptom measures into a format that is friendly and efficient for users, while also tracking information related to sleep, exercise, and daily behaviors. Developed by a group of psychiatrists and reproductive psychiatrists, the measure takes 30-60 seconds to complete. Users use a sliding scale to indicate the degree of each symptom or behavior present within the last 24 hours.

#### GAD-7

The GAD-7 [17] is a 7-item self-report measure assessing symptoms of anxiety. Responders indicate the frequency of symptoms on a scale of 0=not at all to 3=nearly every day, with total scores running from 0 to 21. A score of 0-4 indicates minimal anxiety, 5-9 indicates mild anxiety, 10-14 indicates moderate anxiety, and 15-21 indicates severe anxiety. Spitzer et al [17] found that the GAD-7 exhibited reliable sensitivity (89%) and specificity (82%), validating its effectiveness as a screening tool for generalized anxiety disorder.

